In summary, preliminary investigations of ACT in the treatment of adult anxiety have produced promising results. Other studies have also supported the use of mindfulness - one of the six ACT core processes - in the treatment of childhood anxiety, which suggest that approaches employed within ACT appear to be suitable for child populations. To the best of our knowledge, this will be the first randomized controlled trial to examine the effectiveness of ACT in young people with a diagnosed anxiety disorder. Given the popularity and use of ACT in clinical practice [10], it is imperative that this form of intervention be empirically evaluated for its efficacy. Thus, the aim of this research is to examine the effectiveness of a manualized ACT group-therapy program in the treatment of anxiety disorders among children and adolescents. It is hypothesized that ACT will be at least as effective in the treatment of anxiety disorders in these populations relative to a manualized CBT group-therapy program, and that ACT will be more effective in the treatment of anxiety disorders in this population relative to the control condition at both immediate post-treatment and at three-month follow-up on outcome measures. The secondary aim of the trial concerns the adolescent participants and is to identify the mechanisms of change surrounding the intervention that are critical to changes in outcome measures. It is hypothesized that these will include decreased experiential avoidance and cognitive fusion, as well as increased emotional awareness, acceptance and valued living.

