### Participants

Participants will be approximately 150 children (90 younger and 60 older children) aged 7 to 17 years with a primary diagnosis of a Diagnostic and Statistical Manual of Mental Disorders (DSM-IV) anxiety disorder. The participants will be age-classified as ‘children’, aged 7 to 11 years, and ‘adolescents’, aged 12 to 17 years. Twelve years of age was determined as the cut-off point to be consistent with other research involving ACT as a treatment for problems among adolescents [20].

Participants will be recruited via referrals to the Department of Psychological Medicine, The Children’s Hospital at Westmead (CHW), Sydney, NSW, Australia. Referrals will be accepted from anyone, including health professionals (general practitioners, psychologists, pediatricians), educational providers, and self-referrals. Written informed consent will be obtained from the parent or caregiver of the children and from the child/adolescent. Ethical approval was obtained for this study from the Human Research Ethics Committee at CHW and at The University of Newcastle.

The researchers predict that the majority of referrals will come from school counselors, followed by word of mouth, then via parents’ referral through the CHW intake phone line. In terms of proportions, it is expected that 60% to 70% of referrals will come from school counselors. On the basis of recruitment efforts to date and requests to intake phone line, the researchers consider that the anticipated sample will be achieved.

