### Sample size calculation

A power analysis was conducted to determine the approximate sample size required to achieve an examination of the effectiveness of a manualized ACT group-therapy program, the most sensitive aim. At a power level of 0.8, with an effect size (ES) of 0.6 to 0.7, it is estimated that a minimum 30 participants in each group is required to detect a significant difference between each of the three groups. The employment of analysis of covariance and mixed model statistical tests for pre versus post comparisons will also offer increased power to detect significant differences. The estimated ES of 0.6 to 0.7 is based on the results of three previous meta-analyses of ACT. In terms of primary outcome measures, Hayes *et al*. [31] observed that, compared to structured interventions, ACT was superior after treatment (*d* = 0.48) and at follow-up (*d* = 0.63). Ost [71] found that ACT was superior to established treatments achieving a mean ES of 0.68. In contrast, Powers *et al*. [72] found that, on primary outcome measures, ACT achieved ES in the range *g* = 0.42 to 0.68 when ACT was compared with control or waitlist conditions and *g* = 0.18 compared to established treatments. The ES for the current study is estimated in line with the higher-end ES results achieved across the aforementioned meta-analyses. The rationale for this is that these meta-analyses have incorporated studies for a range of low-prevalence disorders - disorders that are typically considered to be treatment resistant - whereas the current study focuses only on anxiety, high prevalent disorders, widely acknowledged to be more responsive to treatment.

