### Statistical analysis

Data coding and analysis will be conducted using the IBM SPSS Statistics v.21 software program. Primary outcome measures will be examined both with intention-to-treat analyses and analyses conducted on treatment completers. For the efficacy hypotheses, paired t-tests and linear mixed models will be used to investigate changes in pre versus post primary and secondary outcome measures. Statistical significance will be considered as *P <*0.05. The mixed model approach has been selected as it allows for inter-participant and intra-participant variance as well as the inclusion of participants with missing data, whilst maintaining power.

In accordance with the protocol of Forman *et al*. [70], mechanism of change hypotheses will be examined using correlation and independent t-tests to determine which variables to include in a multivariate analysis of variance. Post-hoc multiple comparisons (for example, Bonferroni correction) will be performed to determine where significant differences lie. Multivariate regression examining factors related to treatment success will also be employed and will include examining any demographic (such as age, gender, family functioning) and clinical (such as pre-scores, psychological flexibility) factors that might be related to outcomes. Mediational analysis, a regression-based approach, will be used to test hypotheses about the mechanisms behind outcome, as this is a powerful way of determining mechanisms by which an effect operates rather than the existence of an effect [73]. It allows for more than one mediator and adjusts all paths for the potential influence of covariates not proposed to be mediators in the model. Receiver operating curve plots of the true positive and false positive rate for different possible cut-points of the regression test will be conducted because receiver operating curves convey information relating to the trade-off between sensitivity and specificity, and maximize predictive value. The coordinates of the receiver operating curve will be used to determine the optimal cut-point for the test. The full information maximum likelihood method will be used to deal with missing data.

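### No deciding contrast or time point is named for efficacy: the stated ACT hypotheses share an undivided 5%, so familywise error on one endpoint is about 9% to 13% in the pooled sample (12% to 16% with CBT v waitlist)

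*Protocol article*

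**What the plan says.** The Background gives two efficacy hypotheses. The first is that "ACT will be at least as effective in the treatment of anxiety disorders in these populations relative to a manualized CBT group-therapy program". The second is that ACT is superior "relative to the control condition at both immediate post-treatment and at three-month follow-up on outcome measures". Neither hypothesis and neither time point is ranked above the other.

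Sample size calculation describes the effectiveness of the ACT program as its most sensitive aim but names no comparator. It then sizes the trial "to detect a significant difference between each of the three groups", which is three arm pairs and so includes CBT v waitlist.

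Statistical analysis sets one threshold in its efficacy paragraph: "Statistical significance will be considered as *P <*0.05". It gives no order, gate or split. The one correction appears in the next paragraph, for the adolescent mechanism analysis, after a multivariate analysis of variance: "Post-hoc multiple comparisons (for example, Bonferroni correction) will be performed to determine where significant differences lie".

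Follow-up assessment provides the three-month visit for the two intervention groups only, and Controls says that the waitlist group receives CBT after 10 weeks.

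On the population, "Participants will be approximately 150 children (90 younger and 60 older children) aged 7 to 17 years". Study design describes a group-by-time layout without an age factor.

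**The concern.** The contrasts can disagree. ACT might beat the waitlist and not differ from CBT, or differ from CBT at three months but not at post-treatment. With nothing ranked, any of these could be presented as the trial's efficacy result at full alpha, chosen after the data are seen. The secondary, mechanistic aim carries a correction while the three-arm efficacy comparison carries none.

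The choice also affects what the trial can show. Sample size calculation cites one meta-analysis that put ACT at 0.42 to 0.68 against control or waitlist but at 0.18 against established treatments. The two ACT contrasts are therefore very different questions at the same sample size.

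**Working it through.** **1. The plan's own figure.** Inputs from Sample size calculation: "At a power level of 0.8, with an effect size (ES) of 0.6 to 0.7", and "a minimum 30 participants in each group is required". Formula per arm: n = 2(z_alpha + z_power)² / d².

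- Two-sided 5%: 2(1.960 + 0.842)² = 15.70. Dividing by 0.6², 0.65² and 0.7² and rounding up gives 44, 38 and 33.
- One-sided 5%: 2(1.645 + 0.842)² = 12.37, which gives 35, 30 and 26.

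The stated 30 is matched at one-sided 5% and the midpoint effect of 0.65. An omnibus three-group test with one arm differing by 0.7 comes close, at 31. In either case the figure carries no allowance for three pairwise claims.

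**2. Which between-arm tests exist.** At post-treatment there are three pairs: ACT–CBT, ACT–waitlist and CBT–waitlist. At three months only ACT–CBT has both arms assessed under randomized conditions. That makes four feasible tests per endpoint, of which three come from the stated hypotheses.

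**3. Familywise error on one endpoint, all nulls true, each test two-sided at 0.05.** With equal arms, Z_ij = (e_i − e_j)/√2, so two contrasts that share an arm correlate at 0.5. For the three post-treatment pairs the rate is the chance that the studentized range of three exceeds 1.96 × √2 = 2.772, which is 0.122 (if independent, 1 − 0.95³ = 0.143). The other rows come from 2,000,000 simulated draws. The post/follow-up correlation is not in the document; it is taken as 0.5, with 0.3 to 0.7 as the range. The last column is 1 − (1 − p)² and applies only if efficacy were tested separately in two age groups.

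| Tests counted | Pooled, p | If split by age |
|---|---|---|
| Two ACT contrasts, post | 0.09 | 0.17 |
| The same plus ACT–CBT at three months | 0.129 (0.122 to 0.133) | 0.242 (0.230 to 0.249) |
| Three pairs, post | 0.122 | 0.230 |
| The same plus ACT–CBT at three months | 0.159 (0.152 to 0.163) | 0.293 (0.280 to 0.300) |

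**4. Power of the candidate primary contrast.** Equal allocation gives 150/3 = 50 per arm pooled. Two-sided 5% power is 0.84 at an effect of 0.6 and 0.93 at 0.7. At the cited 0.18 against established treatments it is about 0.14. These figures are before dropout and before any clustering by therapy group.

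**The case against.** The strongest reply is that this is a condensed article and a separate analysis plan may order the tests. A plain 5% threshold does not exclude a gate, and with three arms an overall group test before the pairwise tests would hold the error near 5% (0.051 gated against 0.124 ungated in a simulation at 50 per arm). That stands as a limit on the numbers, which are conditional on ungated testing. It does not remove the point. The protocol itself commits to differences between every pair of arms, to two time points and to an undivided threshold, and it places its only correction elsewhere. The deciding contrast also drives the sample size, so it belongs in this document.

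Three further objections hold in part.

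- CBT v waitlist is not a hypothesis; it comes only from the sizing sentence. Without it the range is still 9% to 13%.
- The planned efficacy analyses are paired t-tests and mixed models, and some primary outcomes are diagnostic or categorical. The simulated z-tests therefore approximate the between-arm contrasts and do not reproduce the planned analysis.
- The ACT v CBT hypothesis is of non-inferiority type. The rates above count false differences, which is all that a 5% difference test can yield. A false non-inferiority rate cannot be computed without a margin.

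A reader might infer that efficacy will be tested separately in children and adolescents. The age groups receive different programs, the hypotheses refer to populations in the plural, and 90 children is 3 × 30. But no sentence says so, the design has no age factor, and age appears only among candidate factors in a regression. A reader might also count 3 × 2 × 2 = 12 tests, but no untreated waitlist remains at three months.

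**Conclusion.** The concern holds in a limited form. The protocol names no deciding contrast or time point and applies an undivided 5% to each. On one endpoint in the pooled sample, familywise error is about 9% to 13% for the stated ACT hypotheses and 12% to 16% with CBT v waitlist added, which is roughly two to three times the nominal level. This assumes two-sided, ungated tests, equal arms, and a post/follow-up correlation of 0.3 to 0.7.

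The 17% to 30% range belongs only to separate testing by age. It should not be quoted as a property of this plan.

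One hypothesis, ACT against control at three months, cannot be tested against untreated participants under the schedule described in Follow-up assessment and Controls.

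**What to change.** In Statistical analysis, name one primary comparison. One workable choice is ACT v waitlist at the 10-week post assessment, in all randomized participants pooled, from the mixed model with age group as a factor, at two-sided 5%. Then:

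- Make ACT v CBT the key second comparison, after the primary in a fixed order. Report it as an estimate with a 95% confidence interval at post-treatment and at three months.
- Support the hypothesis that ACT is no worse than CBT only against a prespecified non-inferiority margin. Do not make the three-month result depend on a significant difference at post-treatment. If ACT and CBT are about equal, such a gate would normally close, although that outcome agrees with the hypothesis.
- Report CBT v waitlist and results by age group as supportive, with an age-by-treatment interaction.
- In the Background, remove or reword the ACT v control hypothesis at three months.
- In Sample size calculation, replace the reference to every pair of groups with the named contrast.

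The cost is wording and the choice and justification of a margin; no extra participants or data are needed. The downside is that CBT v waitlist and the by-age results lose confirmatory status. The change controls error across arms and times for one endpoint only. The several primary measures need their own rule.

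### The extra power credited to analysis of covariance is not secured, because the efficacy analysis omits it and does not say how baseline enters the mixed model

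*Protocol article*

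**What the plan says.** Protocol article, Sample size calculation: "At a power level of 0.8, with an effect size (ES) of 0.6 to 0.7", the section concludes that "a minimum 30 participants in each group is required to detect a significant difference between each of the three groups". It then adds: "The employment of analysis of covariance and mixed model statistical tests for pre versus post comparisons will also offer increased power". No pre-post correlation or variance reduction is given.

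Protocol article, Statistical analysis: for the efficacy hypotheses, "paired t-tests and linear mixed models will be used to investigate changes in pre versus post primary and secondary outcome measures". The mixed model is justified by its handling of variance within and between participants and of missing data. Analysis of covariance is not mentioned. Baseline scores appear only as candidate factors in a separate regression on treatment success.

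Protocol article, Background: the efficacy hypotheses compare ACT with CBT and ACT with the control condition, "at both immediate post-treatment and at three-month follow-up on outcome measures". Both are between-arm comparisons.

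**The concern.** The article names its pre-post methods in two neighbouring sections, and the lists differ. Analysis of covariance earns credit for power in one and is absent from the other, where paired t-tests stand beside the mixed model. A paired t-test compares participants with themselves within an arm, so it can test neither hypothesis in the Background.

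That leaves the mixed model as the only listed between-arm test. Described as investigating change in a three-group by three-time repeated measures design, it can be read as a group-by-time model with baseline as one of the outcome rows. With one pre and one post score, that is a comparison of change scores, which is less precise than adjusting for baseline and, at low correlation, less precise than ignoring baseline. At stake are the precision of ACT v waitlist and ACT v CBT on the continuous scores, and protection against chance baseline imbalance, which a change-score comparison leaves to act through regression to the mean.

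**Working it through.** **Inputs from the article.** Power 0.8; effect size 0.6 to 0.7; minimum 30 per group; significance at P below 0.05, sidedness not stated; total 150.

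**Assumptions.** Two-sided 5%; effect size d = 0.65 (midpoint of the stated range), in units of the post-treatment SD; equal SDs at both visits; equal allocation, so 150/3 = 50 per arm; pre-post correlation r of 0.3 to 0.7. Complete data, no clustering by therapy group, one pairwise contrast at a time.

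**The plan's own figure.** For a plain two-sample comparison of post scores, n per arm ≈ 2(1.960 + 0.842)²/d². Two-sided this gives 44, 38 and 33 for d = 0.6, 0.65 and 0.7, so 30 is not reproduced. One-sided, with 1.645 in place of 1.960, it gives 35, 30 and 26, so 30 appears at d = 0.65. Two-sided t-test power at 30 per arm is 63%, 70% and 76% for the three effect sizes.

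**Variance under each analysis** (outcome SD = 1):
- post scores alone: 1
- change scores, or an unconstrained group-by-time mixed model: 2(1 − r)
- baseline as covariate, or a mixed model with baseline means constrained equal: 1 − r²

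The ratio of the third to the second is (1 − r²)/[2(1 − r)] = (1 + r)/2. It is 0.65, 0.75 and 0.85 at r = 0.3, 0.5 and 0.7, so baseline adjustment needs 35%, 25% and 15% fewer participants than a change analysis for equal precision.

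**Effective effect size** at d = 0.65:
- r = 0.3: change 0.65/√1.4 = 0.549; adjusted 0.65/√0.91 = 0.681
- r = 0.5: change 0.65/√1.0 = 0.650; adjusted 0.65/√0.75 = 0.751
- r = 0.7: change 0.65/√0.6 = 0.839; adjusted 0.65/√0.51 = 0.910

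**Power** (noncentral t, two-sided 5%):

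| n per arm | r | Change | Baseline-adjusted | Gap (points) |
|---|---|---|---|---|
| 30 | 0.3 | 0.55 | 0.74 | 18.5 |
| 30 | 0.5 | 0.70 | 0.82 | 11.9 |
| 30 | 0.7 | 0.89 | 0.93 | 4.2 |
| 50 | 0.3 | 0.78 | 0.92 | 14.5 |
| 50 | 0.5 | 0.90 | 0.96 | 6.5 |
| 50 | 0.7 | 0.99 | 0.995 | 0.9 |

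Post scores alone give 0.70 at 30 per arm. The change analysis therefore loses power against that benchmark at r = 0.3, equals it at r = 0.5 and beats it at r = 0.7.

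**Sensitivity.** By the normal approximation, over d = 0.6 to 0.7 and r = 0.3 to 0.7 the gap runs from 2.9 to 18.5 points at 30 per arm and from 0.4 to 16.4 at 50. At r = 0.8, d = 0.65 and 30 per arm it is about 1 point. A generalised least squares check with two or three time points under compound symmetry gave the constrained-baseline mixed model exactly the analysis-of-covariance variance, so its gap is 0.

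**The case against.** The strongest reply is that the sizing sentence credits analysis of covariance and mixed models jointly, and the mixed model is in the analysis section. Fitted with baseline as a covariate or constrained, it loses nothing. Investigating change may describe the question rather than the response variable, and how baseline enters a model is detail an article can leave to a fuller plan. This stands, and it limits the point to a gain that is not secured.

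A reader might infer more in four ways, none supported by the documents:
- That the gain is definitely lost, or the power statement false. The model specification is open, and even a change analysis gains power over post scores when r exceeds 0.5. No correlation is given.
- That the sample size depends on analysis of covariance. The gain is described as additional to the 30 per group, and no variance reduction is shown entering the calculation.
- That 30 per group is itself wrong. It does not reproduce two-sided, but a one-sided test at 0.65 gives 30, and sidedness is not stated.
- That the pre-versus-post wording leaves out three months. The design has two post-treatment assessments, and the phrase can cover both.

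It is also fair that the formulas apply to continuous scores, whereas the Primary outcome measures section defines the primary outcomes as diagnosis and a shift between severity ranges.

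The reply does not remove the mismatch between the two lists, nor make a paired t-test a test between arms.

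**Conclusion.** The two sections name different efficacy methods. One of the listed methods cannot test the hypotheses, and the baseline adjustment that would secure the credited gain is not stated. For the continuous scores, the cost is conditional. If the mixed model is run as an unconstrained change analysis, power is about 4 to 18 points lower than with baseline adjustment at 30 per arm and about 1 to 15 points lower at about 50 per arm. This rests on effect size 0.65, two-sided 5% and an assumed correlation of 0.3 to 0.7. If baseline is already a covariate or constrained, the cost is zero. The figures say nothing about power for the categorical primary outcomes. The change is worth making because it costs nothing and closes off the inefficient reading.

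**What to change.** In Statistical analysis, state that for the continuous ADIS-IV severity, MASC and CBCL scores the efficacy test is a linear mixed model with the baseline score as covariate, or with baseline means constrained equal across arms. Report adjusted between-arm differences at 10 weeks for all three arms and at three months for ACT v CBT only, since the Follow-up assessment section schedules the three-month visit for the two intervention groups alone. Keep paired t-tests as descriptive summaries of within-arm change. In Sample size calculation, name this same analysis as the source of any extra power.

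The cost is wording only: baseline scores are already collected from every participant. The categorical primary outcomes need their own stated analysis, which this change does not supply.

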### CBT program - Cool Kids (ages 7 to 11 years) and Chilled® (ages 12 to 17 years)

The CBT program will comprise the Cool Kids and Chilled® Programs developed at the Centre for Emotional Health, Macquarie University [66]. The effectiveness of Cool Kids and Chilled® in treating anxiety has been empirically demonstrated [66]. Cool Kids and Chilled® assist children and adolescents, respectively, to learn skills to recognize their emotions and combat anxiety, encouraging brave behavior and gradual engagement with feared situations. Because CBT is currently the most empirically supported therapeutic approach for children and adolescents [8], it was determined to be the most stringent comparison condition to employ within this trial. The ‘worry wave’ section of the Cool Kids and Chilled® Programs will be omitted for the purposes of this research as it was considered to have mindfulness components more consistent with an ACT approach. This is a small component of the overall program.

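### The 80% power claimed for every pair of arms is unsupported for ACT versus CBT, where the protocol's own cited effects run from 0.18 to 0.68

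*Protocol article*

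**What the plan says.** All references are to the protocol article.

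- **Sample size calculation, inputs.** "At a power level of 0.8, with an effect size (ES) of 0.6 to 0.7", the section concludes that "a minimum 30 participants in each group is required to detect a significant difference between each of the three groups". One effect-size range serves all three pairs of arms, so ACT versus CBT is covered.
- **Sample size calculation, sources.** "The estimated ES of 0.6 to 0.7 is based on the results of three previous meta-analyses of ACT". Against structured or established treatments these give 0.48 after treatment and 0.63 at follow-up (first meta-analysis), 0.68 (second) and 0.18 (third). Against control or waitlist the third gives 0.42 to 0.68.
- **Sample size calculation, choice.** "The ES for the current study is estimated in line with the higher-end ES results achieved across the aforementioned meta-analyses". The reason offered is that the meta-analyses included treatment-resistant disorders, whereas anxiety is held to respond better to treatment. The section adds that analysis of covariance and mixed models will increase power.
- **Background, last paragraph.** Superiority of ACT is hypothesised over the control. Against CBT the hypothesis is that "ACT will be at least as effective in the treatment of anxiety disorders in these populations relative to a manualized CBT group-therapy program".
- **CBT program.** CBT was chosen as comparator because "it was determined to be the most stringent comparison condition to employ within this trial".
- **Statistical analysis.** "Statistical significance will be considered as *P <*0.05"; sidedness is not stated.

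**The concern.** The two contrasts involving ACT ask different questions. Against a waitlist, a large effect is plausible and superiority is hypothesised. Against CBT, which the protocol presents as the hardest comparator available, the hypothesis is only that ACT is no worse. Yet both are powered on the same 0.6 to 0.7.

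The argument for the upper end does not carry over to ACT versus CBT. If anxiety responds well to psychological treatment, it should respond to CBT too. That may raise the effect of each therapy against no treatment, but it gives no reason to expect a wider gap between the two.

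At stake is the interpretation of the head-to-head result. The abstract promises evidence on the comparative effectiveness of the two therapies. A reader who takes the stated 80% at face value would give a non-significant difference more weight than a trial of this size can support.

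**Working it through.** **Inputs.** Power 0.80, effect 0.6 to 0.7 and 30 per group come from Sample size calculation; the 0.05 level comes from Statistical analysis. The total of 150 comes from the abstract and Participants; 50 per arm is 150/3 and assumes equal allocation with no dropout. Two-sided testing is my base case. Effects are standardised, so SD = 1.

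**Formulas.** With n per arm and effect d:
- Power is that of a two-sample t-test with 2n − 2 degrees of freedom and noncentrality d × √(n/2).
- Approximate size for 80% power, two-sided: n = 2 × ((1.96 + 0.8416)/d)². The exact t-test needs about one more per arm.
- With analysis of covariance at baseline correlation r, replace d by d/√(1 − r²).
- Approximate 95% confidence interval half-width: 1.96 × √(2/n).

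**Step 1: the plan's own figure.** A one-sided 0.05 test at d = 0.65 needs 30 per group, so the stated number can be reproduced that way. A two-sided t-test needs 45, 39 and 34 per group at 0.6, 0.65 and 0.7; 30 per group then gives 63%, 70% and 76%. Analysis of covariance could also bring the number to 30 (for example d = 0.7 with r = 0.3), but the section states neither a one-sided test nor a correlation as an input.

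**Step 2: ACT versus CBT at the cited active-comparator effects** (unadjusted, two-sided 5%). Noncentrality is 3.873 × d at n = 30 and 5 × d at n = 50.

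| Cited effect | Noncentrality, n = 30 | Power, n = 30 | Noncentrality, n = 50 | Power, n = 50 |
|---|---|---|---|---|
| 0.18 | 0.70 | 10.5% | 0.90 | 14.5% |
| 0.48 (post) | 1.86 | 45% | 2.40 | 66% |
| 0.63 (follow-up) | 2.44 | 67% | 3.15 | 88% |
| 0.68 | 2.63 | 74% | 3.40 | 92% |

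For 80% power, d = 0.18 needs 2 × (2.8016/0.18)² = 484.5, so 485 per arm (486 by t-test). d = 0.48 needs 2 × (2.8016/0.48)² = 68.1, so 69 per arm (70 by t-test).

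**Step 3: sensitivity to the test.** One-sided 0.05 at 30 per arm gives 17% at 0.18, 58% at 0.48, 78% at 0.63 and 83% at 0.68.

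For analysis of covariance the article gives no correlation, so I assume r = 0.5 to 0.6. Then √(1 − r²) is 0.866 to 0.8, and 0.48 becomes 0.554 to 0.600 while 0.18 becomes 0.208 to 0.225.
- At 50 per arm, power is 78% to 84% at 0.48 and 18% to 20% at 0.18.
- At 30 per arm, it is 56% to 63% at 0.48 and 12% to 14% at 0.18. At the two upper effects it is 79% to 85% (0.63) and 85% to 90% (0.68).
- Reaching 80% at 30 per arm would need r of about 0.75 for 0.48 and 0.97 for 0.18.

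**Step 4: precision for ACT versus CBT.** The half-width is 1.96 × √(2/50) = 0.39 SD at 50 per arm and 1.96 × √(2/30) = 0.51 SD at 30 per arm, unadjusted.

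**Step 5: ACT versus waitlist, for contrast.** Over the cited 0.42 to 0.68, unadjusted two-sided power runs from 36% to 74% at 30 per arm and from 55% to 92% at 50 per arm. The smallest difference with 80% power is 0.74 at 30 per arm and 0.57 at 50 per arm.

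**The case against.** **The sources do not all point down.** Two of the four active-comparator figures, 0.63 and 0.68, lie inside 0.6 to 0.7, and at 50 per arm they give 88% and 92%. The protocol also says openly that it took the upper end. This stands. A reader might infer that the trial cannot have 80% power for ACT versus CBT, but the document does not support that: the sources conflict, and the claim fails at the lower two.

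**No worse includes better.** A reader might say that the 0.6 to 0.7 assumption contradicts the Background hypothesis. It does not, because a large advantage for ACT would satisfy that hypothesis. The mismatch is milder: a calculation for detecting a large difference is attached to a pair for which no such difference is hypothesised.

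**Adjustment adds power.** The section says so, and the unadjusted figures ignore it. This stands in part. With a correlation of 0.5 to 0.6, 50 per arm gives roughly 80% at 0.48, and 30 per arm reaches or nearly reaches 80% at the two upper effects. It does not help at 0.18, or at 0.48 with 30 per arm.

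**Nothing says a null result will be called equivalence.** Correct. A reader might fear that, but the article states no such intention, and a non-significant result is likely only if the true difference is towards the low end.

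**Conclusion.** The point holds in a limited form: 80% power for ACT versus CBT is unsupported across the range of effects the protocol itself cites, though not impossible within it. With 30 per arm, unadjusted two-sided power is 10.5% to 74% over 0.18 to 0.68, so none of the four cited effects reaches 80%. With 50 per arm it is 14.5% to 92%, and 80% is reached only at the upper two.

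The argument does not depend on ranking the meta-analyses. The one reason given for the upper end applies equally to CBT, and the Background does not hypothesise a large gap.

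The figures assume equal allocation, a two-sided 5% test, a standardised continuous outcome and no dropout. Dropout, which the article anticipates without giving a rate, would lower them; baseline adjustment would raise them. Simply confining the 80% claim to ACT versus waitlist over 0.42 to 0.68 would not cure the problem, because step 5 shows that it fails over much of that range too.

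**What to change.** Reword the sample size paragraph; no extra patients are needed.

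1. Delete the claim that 30 per group is enough "to detect a significant difference between each of the three groups".
2. For ACT versus CBT, report power over the cited 0.18 to 0.68 and the expected 95% confidence interval half-width (about 0.39 SD at 50 per arm). Say that the no-worse-than-CBT hypothesis will be judged from that interval, not from a non-significant difference test.
3. For ACT versus waitlist, state that 80% power (unadjusted, two-sided) holds for differences of about 0.57 SD or more at 50 per arm, or about 0.74 SD at 30 per arm, and not over the whole of 0.42 to 0.68.
4. If credit is taken for baseline adjustment, state the assumed correlation.

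The cost is a few sentences. The downside is that the stated power becomes less favourable.
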